#### Alters recruitment

Alters recruitment will be conducted online based on the WeChat mini-program system. Alters will be reached through egos’ shared link. After an ego shares his COHIV with exchange mechanism (intervention group) or without exchange mechanism (control group) to their friends in WeChat, those who click the link will be candidate alters in our study. An online page that provides study details will be presented to the candidate alters after they read the content of ego’s report. Those interested in this study will be asked to complete the screening questionnaire and eligible individuals will fill in an online consent form (Additional file 2) and become alters.

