### Participants

The potential participants are MSM who received exchangeable or regular online COHIV. The recruitment is based on the unit of an egocentric social network (Fig. 5), which includes one core member (ego) and several network members (alters) who connect to this core member. In this study, the ego is defined as one MSM people who tests HIV at the Lingnan Community Support Centre clinic and shares his COHIV via WeChat mini-program to his WeChat contactors, while alters are those contactors who receive and read the shared report. An ego and his alters are considered as a cluster in this trial. Our intervention is targeting alters, whereas egos are the recruiters of MSM alters.

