### Intervention

#### Intervention group with exchangeable COHIV

An exchange mechanism is developed as the extension to the above-mentioned WeChat-based HIV Testing Service System platform. In the procedure of the online COHIV exchange (Fig. 6), after alter A in the intervention group clicked “B’s HIV Test Result”, a WeChat mini-program link, from his WeChat contactor B, A will see the message that “Please send your HIV Report to B, only then you will be able to read B’s HIV Report''. Alter A will be invited to make an appointment for the HIV testing service, and linked to the *Appointment Service* module (Fig. 2). If A has the WeChat-based online COHIV, he will be able to see B’s result after sending his own and vice versa. Since there is no time frame for COHIV exchange, the most recent COHIV will be exchange between A and B if both sides have it. The most recent test date is on the COHIV. We hypothesize that MSM will be motivated to get tested if he is interested in sender as well as the sender's HIV result.

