#### Control group with regular COHIV

The regular COHIV without exchange mechanism is as usual service. Based on the established WeChat-based HIV Testing Service System (Figs. 2, 3, 4), MSM can share their COHIV (Fig. 4) with any WeChat contactors. Alters in the control group will see the content of the regular COHIV directly after they click the result shared by the ego. At the end of the HIV test result, the system will guide alters about how to get an HIV test by arranging appointments with a MSM friendly clinic and link to the WeChat-based *Appointment Service* module (Fig. 2). The procedure of alters in the control group receiving the certified HIV result is shown in Fig. 7.

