### Outcomes and data collection

The following outcomes are collected at the time of intervention and 3, 6, 9 months in the post-intervention period. Data will be collected every three months by four ways: (1) online surveys to alter participants; (2) surveys administered to egos; (3) routinely collected data in the HIV testing service system of Guangzhou CDC; (4) data recorded through the WeChat-based data portal (Fig. 1). Online surveys to alters include baseline and follow-up questionnaires. The baseline questionnaires are assigned to alters when they click egos’ reports via the WeChat mini program. The 3, 6, 9 months post-intervention follow-up questionnaires on alters will be carried out and audited via the survey website named Wenjuanxing and via WeChat. If a questionnaire has paradoxical answers, researchers will check the answers with the alter via WeChat. Incentives (Red Envelopes) on WeChat will be given to alters every time when they finish answering and checking questionnaires. Alters will receive 50 RMB(≈ 7.5 USD) for the baseline survey, and then receive 50 RMB(≈ 7.5 USD) for the first follow-up, 20 RMB to 100 RMB(≈ 3 USD to 15.5 USD) randomly for the second and third follow-ups respectively.

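### The protocol gives two incompatible enrolment points for alters; the one in the recruitment text would select intervention alters, but not controls, on holding an HIV report

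*Protocol article*

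**What the plan says.** **Enrolment after reading.** Participants defines the study population so that "alters are those contactors who receive and read the shared report". Alters recruitment is consistent with this: the study page "will be presented to the candidate alters after they read the content of" the ego's report. Screening and online consent come after that page, and only then does the contact become an alter.

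**What reading requires in each arm.** In the section on the control group: "Alters in the control group will see the content of the regular COHIV directly after they click" the shared result. In the section on the intervention group, the contact first meets the message "Please send your HIV Report to B, only then you will be able to read B’s HIV Report". The same section adds: "If A has the WeChat-based online COHIV, he will be able to see B’s result after sending his own and vice versa". It sets no age limit on the report exchanged.

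**Enrolment at the click.** Outcomes and data collection says otherwise: "The baseline questionnaires are assigned to alters when they click" the ego's report.

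**Eligibility.** Inclusion and exclusion criteria admits alters whose HIV status is unknown or negative and makes no distinction by arm.

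**The concern.** Egos are randomised, but the primary outcome is measured in alters, who join after their ego has been allocated. Any step between allocation and enrolment that works differently in the two arms can therefore undo the randomisation.

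On the enrolment-after-reading text, such a step exists. A man with no certified report who receives a control link can read, be invited and enrol. The same man receiving an intervention link must first test and obtain a report. If he declines, he is never invited. The mechanism is meant to move exactly this man.

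Two consequences follow on that reading:

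- **Selection.** The intervention sample consists of men who had already tested or who tested on being prompted. The control sample is not filtered in this way. Men who were never invited are in no data set, so neither the intention-to-treat rule nor the multiple imputation in Statistical analysis can bring them back.
- **Timing.** A test prompted by the link would fall before consent and baseline. It would be recorded as baseline testing rather than as follow-up outcome, which removes true effect.

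The first tends to inflate the estimated effect and the second to shrink it.

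**Working it through.** **1. Which enrolment point does the text support?**

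| Section | Implied enrolment point |
|---|---|
| Participants | After reading |
| Alters recruitment | Study page, screening and consent after reading; but contacts are candidates from the click |
| Intervention group | The man is already called an alter when he meets the lock, before any exchange |
| Outcomes and data collection (baseline) | At the click |
| Outcomes and data collection (report delivery) | Proportions of alters who read the ego's report and who obtain their own. If enrolment followed reading, the first would be 100% in both arms and the second 100% in the intervention arm |
| Statistical analysis | Subgroup by whether the alter exchanged with the ego. If enrolment followed reading, this would merely duplicate arm |

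The two groups of statements cannot both be right. Fig. 6, which shows the intervention-arm procedure, is not available here, so the system's actual behaviour cannot be confirmed.

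**2. The plan's own sample size.** Inputs from Sample size and statistical power: 20% in control, a 10-point effect (so 30%), 80% power, ICC 0.2 and 2 alters per network; two-sided 0.05 from Statistical analysis. The pooled two-proportion formula gives 293.15 per group. The design effect is 1 + (2 − 1) × 0.2 = 1.2. Then 293.15 × 1.2 = 351.8 alters, or 175.9 networks (stated: 352 and 176). For 30% loss, 176 / 0.7 = 251.4, so 252 egos and 504 alters, as stated. The sample size is not in question.

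**3. Size of the selection if reading gates enrolment, with no true effect.** Neither model's key inputs are in the documents.

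*Model A.* Assume 20% of all clickers test per three months in both arms, a share h of intervention clickers hold a report, and holders test RR times as often as non-holders. Only holders enrol in the intervention arm. Then:

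- non-holder rate = 0.20 / (h × RR + 1 − h)
- holder rate = RR × non-holder rate
- spurious difference = holder rate − 0.20

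Example with h = 0.5 and RR = 3: 0.20 / (1.5 + 0.5) = 0.10; 3 × 0.10 = 0.30; difference 10.0 points.

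The rejection rate uses a two-sided Wald test with effective n = 352 / 1.2 = 293 per arm.

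| h | Spurious difference, RR 1.5 to 3 | Rejection rate with no true effect |
|---|---|---|
| 0.9 | 0.7 to 1.4 points | 5.5% to 7% |
| 0.7 | 2.2 to 5.0 points | 10% to 31% |
| 0.5 | 4.0 to 10.0 points | 22% to 80% |
| 0.3 | 6.1 to 17.5 points | 42% to 99.8% |

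With RR = 1 the difference is zero and the rejection rate is 5%.

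*Model B.* Let each man have his own quarterly testing probability, beta-distributed with mean 0.20 and scaled so that 38% test at least once in four quarters (the national past-year figure in Background). This gives concentration M = 1.22 and within-person correlation 1 / (1 + M) = 0.45. Treat holding a report as any test in the last k quarters, and let q be the probability of none. The next-quarter rate among holders is [0.20 − q × 0.20M / (M + k)] / (1 − q). For one year, q = 0.62, and (0.20 − 0.62 × 0.0468) / 0.38 = 0.45.

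| Look-back | Holder rate | Spurious difference from 0.20 |
|---|---|---|
| 1 year | 0.45 | +25 points |
| 2 years | 0.40 | +20 points |
| 5 years | 0.34 | +14 points |
| 10 years | 0.31 | +11 points |

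Neither model includes prompted tests falling before baseline, which act in the opposite direction.

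**The case against.** The strongest reply is that the recruitment sentence is loose wording shared by both arms and that alters were always meant to enrol at the click. The baseline timing, the use of the word alter before any exchange, the report-delivery proportions, the exchange subgroup and the admission of men of unknown status all fit that. This stands. A reader might infer from the recruitment text that the trial does enrol on testing in one arm. The documents do not establish it: they establish a contradiction, one branch of which is seriously biased.

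A reader might also say that enrolment depends on the outcome itself. That is too strong. The gate is a certified report from this WeChat system, of any date. The outcome is any self-reported test in the past three months, self-testing included. The two are closely related but not the same.

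Finally, a reader might take +25 points as the size of the bias. That figure needs a one-year look-back, which the protocol does not set. It also joins a national testing rate to a planning assumption for control alters, which are different populations, and neither measures who holds a report. The objection to a single headline figure is accepted.

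The reply does not remove the defect. The two sections that define and recruit alters still contradict the section that schedules their baseline, on the question of who is in the primary analysis. That is stated text in conflict, not detail left out by condensing.

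**Conclusion.** The point holds as an internal contradiction about when alters are enrolled, with a conditional but serious consequence. If Participants and Alters recruitment are followed, the intervention sample is selected on prior or prompted testing and the control sample is not, and no analysis of the enrolled alters can correct this. If enrolment is at the click, this bias does not arise and the defect is one of wording.

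The size can be given only as a range under assumption, with no true effect: about 0.7 to 17.5 points if 30% to 90% of intervention clickers hold a report and holders test 1.5 to 3 times as often as non-holders, or about 11 to 25 points in the beta-binomial model with a look-back of ten years down to one. Part of both ranges reaches or exceeds the planned 10-point effect. The bias is zero if holders and non-holders test equally often. Because prompted tests before baseline work the other way, neither the sign nor the size of the net bias is known.

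**What to change.** State one enrolment point, identical in both arms, at the click and before either the exchange prompt or the report. Place the study page, screening, consent and baseline questionnaire there. In detail:

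- In Participants, define an alter as an eligible contact who clicks the link and consents, and remove the requirement to have read the report.
- Reword Alters recruitment to agree with Outcomes and data collection.
- Start the 3-, 6- and 9-month clock at that point.
- Keep every consenting eligible clicker in the intention-to-treat set, including intervention alters who never exchange.
- Report the number of clickers by arm, so that differential entry can be seen.

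If the mini-program already enrols at the click, the cost is a wording amendment. If it does not, its screens must also be reordered. The downside is that some candidates may leave before seeing the report; since they would leave before any arm-specific content, this should affect both arms alike.

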### Randomization, blinding and allocation

Clusters will be blocked by egos and allocated 1:1 to the two groups. The random allocation sequence will be generated by using an electronic random number table and embedded in WeChat mini-program. The sequence will be concealed until the intervention is assigned. Egos will be randomly and automatically assigned to the intervention or control group by the mini-program once the online certified HIV report is sent to their WeChat. As a cluster, the group assignment of an alter is determined by his ego. This will be an open-label study in view of the intervention nature, while the statistician and the clinic staff are blinded. Contamination will be avoided by technical means in which alters in one group cannot open the shared link from egos in the opposite group.

### Intervention

#### Intervention group with exchangeable COHIV

An exchange mechanism is developed as the extension to the above-mentioned WeChat-based HIV Testing Service System platform. In the procedure of the online COHIV exchange (Fig. 6), after alter A in the intervention group clicked “B’s HIV Test Result”, a WeChat mini-program link, from his WeChat contactor B, A will see the message that “Please send your HIV Report to B, only then you will be able to read B’s HIV Report''. Alter A will be invited to make an appointment for the HIV testing service, and linked to the *Appointment Service* module (Fig. 2). If A has the WeChat-based online COHIV, he will be able to see B’s result after sending his own and vice versa. Since there is no time frame for COHIV exchange, the most recent COHIV will be exchange between A and B if both sides have it. The most recent test date is on the COHIV. We hypothesize that MSM will be motivated to get tested if he is interested in sender as well as the sender's HIV result.

**Fig. 6 Fig6:**
[figure not shown]
The procedure of alters in the intervention group receiving the HIV report

A user testing was conducted to optimize the design of the exchange mechanism. MSM were invited to provide their feedback of the mini-program, including problems encountered in the daily use of the exchange mechanism and suggestions on improving user experience of navigating between pages of the program. The wording and length of the baseline questionnaire were also checked by MSM to improve the readability of the questionnaire. Necessary modification was made during this period.

#### Control group with regular COHIV

The regular COHIV without exchange mechanism is as usual service. Based on the established WeChat-based HIV Testing Service System (Figs. 2, 3, 4), MSM can share their COHIV (Fig. 4) with any WeChat contactors. Alters in the control group will see the content of the regular COHIV directly after they click the result shared by the ego. At the end of the HIV test result, the system will guide alters about how to get an HIV test by arranging appointments with a MSM friendly clinic and link to the WeChat-based *Appointment Service* module (Fig. 2). The procedure of alters in the control group receiving the certified HIV result is shown in Fig. 7.

**Fig. 7 Fig7:**
[figure not shown]
The procedure of alters in the control group receiving the HIV report

### Outcomes and data collection

The following outcomes are collected at the time of intervention and 3, 6, 9 months in the post-intervention period. Data will be collected every three months by four ways: (1) online surveys to alter participants; (2) surveys administered to egos; (3) routinely collected data in the HIV testing service system of Guangzhou CDC; (4) data recorded through the WeChat-based data portal (Fig. 1). Online surveys to alters include baseline and follow-up questionnaires. The baseline questionnaires are assigned to alters when they click egos’ reports via the WeChat mini program. The 3, 6, 9 months post-intervention follow-up questionnaires on alters will be carried out and audited via the survey website named Wenjuanxing and via WeChat. If a questionnaire has paradoxical answers, researchers will check the answers with the alter via WeChat. Incentives (Red Envelopes) on WeChat will be given to alters every time when they finish answering and checking questionnaires. Alters will receive 50 RMB(≈ 7.5 USD) for the baseline survey, and then receive 50 RMB(≈ 7.5 USD) for the first follow-up, 20 RMB to 100 RMB(≈ 3 USD to 15.5 USD) randomly for the second and third follow-ups respectively.

### Sample size and statistical power

We calculated our sample size using intracluster correlation, number of outcomes, expected effect size, and the power of the study. We assumed that the intracluster correlation coefficient (ρ) was 0.2, that each social network will consist of no less than 2 alters, and that the HIV testing rate among alters in the control group during the three-month follow up will be 20%. Setting the acceptable level of significance at 0.05 and expected effect size as 10%, 176 social networks (176 egos and 352 alters) are needed in each group to identify the effect with 80% power. Assuming 30% loss of follow-up, we plan to recruit 252 egos and 504 alters in each group.

### Statistical analysis

Intent-to-treat analysis will be used to compare the outcome as well as the baseline characteristics of participants between the two groups. For the analysis of primary and secondary outcomes, mixed effect models with networks and individuals as random effects will be used to account for the clustering effect. In the main analysis, the fixed effects for the intervention group, visit number, the intervention group-by-visit number interaction will be included in the model without covariates adjustment. Appropriate link function and distribution will be used. The consistency of treatment effects on the primary outcome will be explored in predefined subgroups, including age, education, level of HIV stigma, number of COHIV received by alter, whether the alter received COHIV from his sexual partner, whether the alter exchanged COHIV with the ego, whether the alter received COHIV screenshot, whether the alter had casual partners, whether the alter had UAI with casual partners.

In the supplementary analysis, models with adjustment for age, education, UAI in the past three months, and other HIV-related health promotion received in the past three months will be performed. Secondly, models with missing data imputation will be also conducted. Missing data will be imputed using the multiple imputation approach. The above analyses are used to compare with the main analysis result to determine the robustness of the intervention effect. All the tests will be conducted using 2-sided tests at 0.05 level of significance.

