#### Egos recruitment

Egos will be recruited at the Lingnan Community Support Centre clinic. MSM who come to HIV testing and meet all the inclusion criteria will be invited as the ego during the post-test counseling. The counselor will explain the difference between HIV reports with and without exchange mechanism in detail. The MSM who agree to participate as the recruiters will complete a written consent (Additional file 1). Each ego will be randomly assigned to the intervention or control group by mini-program. The egos in the intervention group will receive the COHIV with exchange mechanism through the WeChat mini-program while the egos in the control group will receive HIV report without exchange mechanism. Egos will be informed by counselors they can share their HIV reports with friends via WeChat mini-program to recruit alters.

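### The main model is unadjusted and baseline HIV testing is a covariate in no planned model, although alters are recruited after allocation by egos who know their arm

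*Protocol article*

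**What the plan says.** All references are to the protocol article.

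- **Statistical analysis.** The main mixed model has random effects for networks and individuals and fixed effects for group and visit; "the intervention group-by-visit number interaction will be included in the model without covariates adjustment". A supplementary model adjusts for age, education, unprotected anal intercourse and exposure to other HIV health promotion. Baseline HIV testing appears in neither model. The section also plans a comparison of baseline characteristics between arms.
- **Randomization, blinding and allocation.** Egos are allocated "by the mini-program once the online certified HIV report is sent to their WeChat". An alter takes the arm of his ego. The trial is open label; only the statistician and clinic staff are said to be blinded.
- **Egos recruitment.** Counselors explain to egos in detail how the two reports differ. Then "Egos will be informed by counselors they can share their HIV reports with friends via WeChat mini-program to recruit alters".
- **Participants.** Alters are the target of the intervention; egos act as recruiters.
- **Outcomes and data collection.** The "outcomes are collected at the time of intervention and 3, 6, 9 months". The primary outcome is alters' self-reported testing over the preceding three months, so its baseline value will exist.

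**The concern.** Randomisation balances egos. Every analysed alter enters later: an ego who knows which report he holds decides whom to send it to, and the recipient decides whether to join once he has met content that differs by arm. Both steps could depend on whether the recipient is someone who tests.

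The entry sequence adds to the doubt. Under Alters recruitment, the study page appears after the candidate has read the report. Under the section on the intervention group, he can read it only after sending a report of his own. Read literally together, entry in that arm would select on having tested. Outcomes and data collection, however, assigns the baseline questionnaire at the click, so the true entry point is unclear.

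If the arms differ in baseline testing, an unadjusted follow-up comparison carries part of that difference into the effect estimate. The supplementary model, which is meant to show robustness, leaves out the covariate most directly tied to this mechanism. Precision available from data already collected is also forgone.

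**Working it through.** **1. The plan's own figure.** Inputs from Sample size and statistical power: control rate 20%, effect 10 points, 80% power; "We assumed that the intracluster correlation coefficient (ρ) was 0.2"; "each social network will consist of no less than 2 alters". From Statistical analysis: "All the tests will be conducted using 2-sided tests at 0.05 level of significance".

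- Per arm, unclustered: [1.96·√(2·0.25·0.75) + 0.8416·√(0.16 + 0.21)]² / 0.10² = 293.15.
- Design effect: 1 + (2 − 1)·0.2 = 1.2. Then 293.15·1.2 = 351.8, i.e. 352 alters or 176 networks.
- Loss of 30%: 176/0.7 = 251.4, i.e. 252 networks and 504 alters.

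The stated sample size reproduces. With effective n = 352/1.2 = 293.3 per arm, power is Φ[(0.10·√293.3 − 1.200)/0.608] = 80.0%. The point disputes no stated figure.

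**2. Bias in an unadjusted follow-up comparison, no true effect.** Both inputs below are assumptions; the documents give neither.

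- d = difference between arms in the share of alters who tested in the three months before baseline.
- a = difference in follow-up testing between baseline testers and non-testers.
- Bias = d·a. Type I error is by normal approximation at effective n = 293.3 per arm, control rate 20%.

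| a (points) | d = 5 points | d = 10 points | d = 15 points |
|---|---|---|---|
| 20 | 1.0 (6%) | 2.0 (9%) | 3.0 (14%) |
| 30 | 1.5 (7%) | 3.0 (14%) | 4.5 (26%) |
| 50 | 2.5 (12%) | 5.0 (31%) | 7.5 (57%) |

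Cells show bias in percentage points, with type I error in brackets. The range is 10% to 75% of the planned 10-point effect. The sign follows the sign of d, which is unknown.

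**3. Simulation of the middle case** (d = 10, a = 30, no effect; 176 networks of 2 per arm, one follow-up visit, 1,500 runs, logistic models with cluster-robust errors standing in for the planned mixed model).

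- Unadjusted follow-up comparison: rejects in 16%.
- With baseline testing as covariate: rejects in 5%. Here the imbalance was built to act only through baseline testing, so adjustment removes it by construction.
- Baseline treated as a visit, group-by-visit contrast: log-odds −0.37, rejects in 38%. On the percentage scale, the arm gap is 10 points at baseline and 3 at follow-up, so the change contrast is 3 − 10 = −7 points with no true effect.

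The two readings of visit number can therefore be biased in opposite directions by the same imbalance.

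**4. Precision.** Adjusting for a baseline value with correlation r to follow-up multiplies the variance by about 1 − r². With r assumed, at 352 alters per arm and a single visit:

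| r | Effective n per arm, 293.3/(1 − r²) | Power |
|---|---|---|
| 0 (unadjusted) | 293.3 | 80% |
| 0.2 | 305.6 | 82% |
| 0.3 | 322.3 | 84% |
| 0.5 | 391.1 | 90% |

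**The case against.** Four points can fairly be made for the plan.

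**The size is not documented.** This stands. A reader might infer a within-person correlation of 0.45 by combining the 20% quarterly planning rate with the 38% yearly figure in the Background, and hence a definite 4.5-point bias per 10 points of imbalance. The documents do not support that. One figure is a planning value for control alters and the other describes Chinese MSM in general. The answer also depends on the model: an exchangeable beta-binomial gives 0.45, while a first-order Markov chain gives 0.59. The 10-point imbalance is itself assumed.

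**The change contrast is not shown to be underpowered.** This also stands. A reader might take the interaction to have 76% power at r = 0.45, or 60% at r = 0.2. Those figures apply the 1.2 design effect to a change score. With a network random effect that is constant over visits, and no network-by-visit term stated, the network effect cancels. Effective n is then 352/[2(1 − 0.45)] = 320, giving 83%, and 352/[2(1 − 0.2)] = 220, giving 68%. Break-even with the planned design is 2(1 − r) = 1.2, i.e. r = 0.4. The case against the change contrast is its validity under imbalance, not its power.

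**Baseline may be a visit, with details left to an analysis plan not shown.** Study design does list baseline among the comparison times. That leaves the validity problem in place, and the absence of covariates is a stated choice, not a detail omitted.

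**Adjustment can do harm or fall short.** If the baseline item is answered after arm-specific content, it may already reflect the intervention, and adjusting could remove real effect. No covariate removes selection on unmeasured traits. Both points stand and shape the fix.

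**Conclusion.** The concern holds as a weakness in a stated analysis choice. Alters join after allocation through egos who know their arm, the main model cannot respond to an imbalance in their testing history, and the supplementary model omits that history although it is collected. Neither reading of visit number resolves this.

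The direction and size of bias are unknown. The 1.0 to 7.5 points, with type I error of about 6% to 57%, illustrate assumed inputs for an unadjusted follow-up comparison and are not a forecast. The gain in power, from 80% to about 82% to 90%, rests on an assumed correlation of 0.2 to 0.5 and a single follow-up visit. The planned sample size is unaffected. This should be changed, but it does not invalidate the design.

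**What to change.** 1. Define the main model on the 3, 6 and 9 month visits, with group, visit and group-by-visit, plus baseline HIV testing in the past three months, baseline age and baseline education as prespecified covariates. Keep the unadjusted model as supplementary.
2. Take all of these covariates from the baseline questionnaire.
3. Have the mini-program collect the baseline testing item at the click, before any arm-specific content is shown, and reconcile the three descriptions of the entry sequence.

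Drawing the allocation only at an ego's first share, after he has picked recipients, is a possible secondary step, but it would protect only those first recipients.

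**Cost.** The covariates need only a change of wording, and the data are already planned. The timing of the baseline item needs a small change to survey order, and study information and consent would have to come before it. Selection on unmeasured traits remains and should be acknowledged as a limitation.
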